## Abstract

**Background:**

Chronic pain is a common and frequently disabling problem in older adults. Clinical guidelines emphasize the need to use multimodal therapies to manage persistent pain in this population. Pain self-management training is a multimodal therapy that has been found to be effective in young to middle-aged adult samples. This training includes education about pain as well as instruction and practice in several management techniques, including relaxation, physical exercise, modification of negative thoughts, and goal setting. Few studies have examined the effectiveness of this therapy in older adult samples.

**Methods/Design:**

This is a randomized, controlled trial to assess the effectiveness of a pain self-management training group intervention, as compared with an education-only control condition. Participants are recruited from retirement communities in the Pacific Northwest of the United States and must be 65 years or older and experience persistent, noncancer pain that limits their activities. The primary outcome is physical disability, as measured by the Roland-Morris Disability Questionnaire. Secondary outcomes are depression (Geriatric Depression Scale), pain intensity (Brief Pain Inventory), and pain-related interference with activities (Brief Pain Inventory). Randomization occurs by facility to minimize cross-contamination between groups. The target sample size is 273 enrolled, which assuming a 20% attrition rate at 12 months, will provide us with 84% power to detect a moderate effect size of .50 for the primary outcome.

**Discussion:**

Few studies have investigated the effects of multimodal pain self-management training among older adults. This randomized controlled trial is designed to assess the efficacy of a pain self-management program that incorporates physical and psychosocial pain coping skills among adults in the mid-old to old-old range.

## Background

### The problem of chronic pain in the elderly

Chronic pain is a common problem in the elderly, and is often associated with significant physical disability and psychosocial problems [1]. Estimates of the prevalence of chronic pain problems among community-dwelling older adults range from 58–70% [1]. The most common painful conditions among older adults are musculoskeletal conditions such as osteoarthritis, low back pain, and previous fracture sites [2]. Chronic pain often results in depression, sleep disturbance, decreased mobility, increased health care utilization, and physical and social role dysfunction [1]. Despite its high prevalence, pain in the elderly often is inadequately assessed and treated [1].

As the United States population grows older, the public health problem of chronic pain and its sequelae will worsen. Projections show dramatic increases in this age group; approximately 25% of the population will be age 65 years or older in 2050. Moreover, by 2030 there will be an estimated 8 million people who are 85 years or older [3]. Thus, there is an urgent and growing need for interventions that are effective in decreasing pain, suffering, and pain-related disability in this group.

### The role of self-management in the treatment of chronic painful conditions

There is substantial empirical evidence that attention to cognitive and behavioral factors, in addition to physiological factors, is necessary for the successful treatment of chronic nonmalignant pain [4,5]. Empirically supported multimodal therapies that incorporate cognitive and behavioral strategies now exist for many chronic pain conditions, including rheumatoid arthritis, osteoarthritis, fibromyalgia, and low back pain [6-10]. These therapies aim to enhance the ability of patients to successfully self-manage their pain, using a variety of techniques. Related approaches and strategies are described under the rubrics "cognitive-behavioral therapy" (CBT), "psycho-educational" or "educational," and "self-management" or "self-help." Although there are variations among these approaches, they share some or all of the following components: education about pain, instruction in the identification and modification of negative thoughts, exercise, communication skills, relaxation training, and physical therapies. The goal of the therapies is to enhance function, improve mood, and decrease pain intensity by changing the emotional, cognitive, and behavioral responses to pain.

Despite their documented efficacy in young to middle-aged samples [9-12], cognitive-behavioral and self-management pain therapies have been little-studied in elderly populations. In one of the first examinations of CBT for elderly patients with pain, 69 outpatients with chronic pain were randomly assigned either to immediate treatment or delayed (wait list) treatment [13]. Approximately half of the sample was over 60 years of age, and age was unrelated to outcome. The intervention resulted in significant decreases in pain interference with daily activities and increases in participants' self-reported ability to cope with pain. Limitations of this study included the fairly small sample size and the lack of intent-to-treat analysis.

Keefe and colleagues [14] evaluated the efficacy of a pain coping skills training (CST) intervention as compared with arthritis education and standard care in decreasing pain and physical and psychological disability among 99 middle-aged to older outpatients with osteoarthritic knee pain. The CST consisted of 10 weekly group sessions focusing on identifying and reducing irrational thoughts, diverting attention away from the pain, and changing activity patterns to manage pain. The CST group showed significantly less pain and psychological disability following treatment as compared with the other two groups. At 6-month follow-up, the CST group showed significantly less physical and psychological disability as compared with the education group and marginally less psychological disability as compared with the standard care group [15]. Although this study provides evidence for the benefits of cognitive-behavioral therapy for older adults, it focused on arthritis patients and not older adults per se. Moreover, the average subject age was 64 years. It is not clear whether these findings would generalize to mid-old (i.e., 75–85 years) and old-old (85 years and older) adults. These groups have been shown to differ from their younger counterparts (i.e., those 65–74 years) in several dimensions, including pain prevalence, physical and cognitive function, involvement in recreational and social activities, and social support [16-19], that potentially could affect the pain experience and response to pain therapies.

One study that examined a cognitive-behavioral therapy in old-old adults (mean age 77.2 years) evaluated the efficacy of a 10-week CBT intervention (n = 11) versus an attention/support (AS) condition (n = 10) for nursing home residents [20]. The CBT condition incorporated pain education, progressive relaxation, imagery, coping skills training, cognitive restructuring, and attention diversion. CBT participants reported significantly less pain and pain-related disability following the intervention, as compared to the AS group. These significant differences were maintained at the 4-month follow-up. This study provides important evidence that CBT can be successfully applied to old-old adults; however, the results need to be replicated in other, larger samples, including non-institutionalized elderly.

### Retirement communities as a study setting

As the U.S. population continues to age, retirement communities have gained popularity. A retirement community allows older adults with varying lifestyles and physical abilities to live in an environment that encourages independence while providing needed access to health and social resources [21]. Although most residents of these communities live independently (some facilities also include assisted living apartments and skilled nursing facilities), the retirement community, on average, represents a mid-old to old-old population that is vulnerable to physical disability, health problems, and social isolation [22]. The growing population in retirement communities, then, is one in which self-management group therapies for chronic pain may hold great promise. Adoption of regular wellness-oriented pain management strategies may contribute to enhanced functioning and prolonged independence.

### Study purpose and specific aims

The primary goal of this study is to evaluate the efficacy of a pain self-management group intervention (SMG), as compared with a control condition (BOOK), in decreasing physical disability, pain, pain-related interference with activities, and depression in older retirement community residents with chronic pain. In addition, we wish to determine the extent to which SMG participation is associated with changes in specific pain-related beliefs and coping strategies, and the extent to which changes in these process variables are associated with changes in outcomes (physical disability, pain intensity, pain-related interference with activities, and depression). We plan to test the following hypotheses:

*1. *At post-treatment and each follow-up, participants assigned to SMG, as compared with participants assigned to BOOK, will report less physical disability (primary outcome), and lower pain intensity, pain-related interference with activities, and depressive symptom severity (secondary outcomes).

*2. *Participants assigned to SMG, as compared with participants assigned to BOOK, will show greater pre- to post-treatment increases in self-efficacy and use of adaptive pain coping strategies and greater decreases in catastrophizing. Significant differences between SMG and BOOK groups in pain-related beliefs and coping strategies will be maintained at 6-month and 1-year follow-ups.

*3. *Pre- to post-treatment changes in specific pain-related beliefs (catastrophizing, self-efficacy) and coping strategies (Chronic Pain Coping Inventory subscales) will be associated significantly with changes in physical and social functioning, pain intensity, and depression over the same period among SMG participants. These changes in beliefs and coping strategies will be maintained at 6-month and 1-year follow-ups.

Figure 1 depicts the hypothesized relationships among study variables.

**Figure 1 F1:**
[figure not shown]
Hypothesized relationships among study variables

## Methods/Design

### Design

This is a currently ongoing randomized controlled trial. The study procedures and measures have been approved by the Swedish Medical Center institutional review board. Figure 2 outlines study procedures and follow-up.

**Figure 2 F2:**
[figure not shown]
Study flowchart

### Participants

Participants (targeted enrollment n = 273) are recruited from residents living in one of the 34 participating retirement communities in Seattle, Washington and the surrounding area. Study inclusion criteria are: (1) 65 years of age or older, (2) pain > 3 months duration that interferes with regular activities; and (3) ability to read and complete study questionnaires in English. Exclusion criteria are: (1) current, active cancer and (2) surgery within the past 6 months or surgery planned in the next 6 months.

### Recruitment and randomization procedures

Participants are recruited using newsletter announcements, flyers, brochures, and informational talks given at each facility. Retirement community residents who are interested in the study are screened to assess eligibility. Eligible residents who provide written informed consent are then asked to complete the baseline measures and to provide the name of their primary care provider (PCP), as well as permission to contact the PCP. PCPs of SMG group participants are sent a letter about the study and asked to contact the research nurse if there is any medical reason to restrict the resident's participation in the exercise portion of the study.

After all participants from a facility have completed the baseline questionnaires, the facility is randomized to receive either the BOOK or the SMG. Randomization is done by facility, rather than by individual participant, for several reasons. First, it expands the number of participating facilities by making feasible recruitment from smaller facilities. If approximately 5% of residents were recruited from any one facility, then it would not be scientifically or financially sound to involve facilities with fewer than 200 residents in independent or assisted living. A pilot study indicated that the ideal self-management group size is 5–12 participants. If we randomized within facilities, at least 10 participants would need to be recruited from each facility to allow 5 SMG participants. However, if all participants within a facility are randomized to the same condition, then smaller facilities can participate. If more than 12 residents in a facility randomized to the SMG condition enroll in the study, more than one group is scheduled. A second advantage of randomization by facility is that there is little risk of participants in one condition talking with participants randomized to another condition about their experiences in the study. Thus, there is less treatment contamination and likelihood that participants from different conditions will compare treatments, a situation that can provoke dissatisfaction among participants who do not receive the treatment of their choice.

### Pain self-management group (SMG)

The SMG intervention, which consists of seven weekly 90-minute group sessions, includes the major components of empirically-supported self-management interventions [23,24], refined for use with the elderly (see Table 1). For example, we include a discussion of myths about pain in older adults (e.g., pain is an inevitable part of aging) and focus on exercises that are effective and safe for older adults with musculoskeletal pain. The intervention is designed to decrease participants' physical disability and pain intensity; increase participation in home, social, and recreational activities; and enhance participants' self-efficacy for managing chronic pain. To accomplish these objectives, the intervention provides basic information about pain management, teaches problem-solving and relaxation skills, and provides practice with a variety of pain management techniques. Participants receive a class syllabus, relaxation tape, Theraband^® ^tubing for the performance of selected exercises, and two hot/cold gel packs.

**Table 1 T1:** Summary of the self-management group intervention

**SESSION NUMBER**: TOPICS	MAJOR CONTENT AND ACTIVITIES
**Session 1**: Introduction; Basic principles of pain	Review purpose of the program/study. Review definition, types, & mechanisms of pain. Discuss myths about pain in older adults. Emphasize goals of chronic pain management. Discuss signs/symptoms that require medical attention. Introduce problem-solving techniques for pain management.
**Session 2**: Role of exercise & physical activity in pain management	Discuss exercise in pain management: problem of de-conditioning, types of exercise, tips for starting exercise program. Demonstrate & practice specific exercises. Introduce relaxation and breathing techniques as effective pain management strategies. Practice progressive muscle relaxation & abdominal breathing.
**Session 3**: Engaging in pleasant, meaningful activities; pacing activities	Discuss ways in which chronic pain may be limiting participation in enjoyable or meaningful activities Use problem solving to develop individualized plans for increasing these activities. Discuss strategies for activity pacing and rationale for avoiding guarding and inactivity. Practice relaxation.
**Session 4**: Challenging negative thoughts; Dealing with pain flare-ups and setbacks	Discuss critical role of thoughts and appraisals about pain in determining affective and behavioral responses to pain. Help participants to identify negative thoughts that they may have in response to pain. Practice challenging negative thoughts with positive thoughts about effective ways to manage pain. Discuss strategies for dealing with setbacks and pain-flare-ups. Practice relaxation.
**Session 5**: Non-drug pain therapies; Heat & cold; Dealing with pain flare-ups and setbacks (continued)	Describe rationale for using nondrug pain therapies. Describe and practice application of heat and cold; review precautions in using heat and cold for pain Continue discussion about coping with pain flare-ups & setbacks in pain management. Practice relaxation.
**Session 6**: Pain medications & complementary therapies	Describe the role of medications for pain management. Discuss the major types of pain medications. Describe the use of complementary therapies in pain management. Discuss steps in making informed decisions about all pain therapies.
**Session 7**: Pain management plan; Wrap-up	Discuss maintenance of gains made through the program. Review coping with set backs & pain flare-ups. Revise written individualized maintenance plans for each participant.

A key component of this self-management group is the development of personalized pain management plans. Participants begin developing a plan during the first class and revise it each week as they learn and practice additional pain management skills. With the assistance of the facilitator and, at times, other group members, participants review pain control strategies that they have learned and practiced and choose one or several strategies that best meet their individual needs and interests. Participants identify specifically what they will do (in measurable terms) and define the parameters (e.g., how many times per week, how far they will walk, how many repetitions of each exercise they will do). Although each person develops his or her own plan, the plans incorporate the same repertoire of activities that are taught in the class. These plans are monitored weekly during the classes and during follow-up phone calls (described below).

### Educational book control condition (BOOK)

Participants who are assigned to the BOOK condition receive a copy of *The Chronic Pain Workbook, 2*^*nd*^*Edition *[25]. Facilitators telephone participants 1 and 4 weeks after participants receive the workbook. The BOOK condition was designed to control for attention and information. In these calls, facilitators inquire about participants' current pain and functioning, and ask about use of pain therapies and self-management techniques. There is no specific therapeutic component in the phone calls and facilitators do not help BOOK participants identify goals or develop a pain management plan.

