### Booster and follow-up phone calls

The SMG group facilitator telephones each participant at 12, 16, 22, and 30 weeks after the final group session. During the booster phone calls, facilitators inquire about pain and functioning, current pain management plans, and successes and obstacles in meeting pain management goals, as well as provide encouragement and assistance in problem-solving obstacles encountered in pain management. BOOK participants receive follow-up phone calls at the same intervals to control for attention.

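### BOOK is described as controlling for attention, but during the intervention phase it provides two phone calls against seven 90-minute group sessions in SMG

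*Protocol article*

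**What the plan says.** The section on the educational book control condition gives its purpose in one sentence: "The BOOK condition was designed to control for attention and information". It describes the contact in that arm as follows: "Facilitators telephone participants 1 and 4 weeks after participants receive the workbook". It then limits the content of those calls: "There is no specific therapeutic component in the phone calls and facilitators do not help BOOK participants identify goals or develop a pain management plan".

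The section on the pain self-management group says that the intervention "consists of seven weekly 90-minute group sessions". Facilitator and peers take an active part: "With the assistance of the facilitator and, at times, other group members, participants review pain control strategies that they have learned and practiced".

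The section on booster and follow-up calls says: "The SMG group facilitator telephones each participant at 12, 16, 22, and 30 weeks after the final group session". BOOK participants are called at the same intervals, again with control for attention as the stated reason.

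The abstract calls the comparator an education-only control. No third arm is described.

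**The concern.** A control for attention should give the comparison group roughly the contact that the intervention group receives, so that contact can be ruled out as the explanation of a difference. In the phase when the treatment is delivered, contact in the two arms differs greatly in amount and in kind: repeated meetings in a group on one side, two telephone calls on the other.

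This matters because of how the outcomes are obtained. The Roland-Morris questionnaire, the Brief Pain Inventory ratings and the Geriatric Depression Scale are all completed by participants. Participants learn their condition; the expectation ratings are collected before they do. The Background section describes retirement community residents as vulnerable to social isolation, so regular group contact could itself shift reported mood and function. The post-intervention assessment, which follows directly on the unequal contact, is one of the three repeated measurements behind the primary group effect.

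At stake is the interpretation of a positive result. If the report repeats that attention was controlled, readers will be entitled to credit the skills taught. Hypotheses 2 and 3, on beliefs and coping, make that reading more inviting.

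**Working it through.** The check uses the contact schedule in the protocol article. The plan gives no contact total of its own to reproduce.

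**Inputs**
- SMG sessions: 7, of 90 minutes each (Pain self-management group).
- BOOK calls in the intervention phase: 2, at weeks 1 and 4; length not stated (Educational book control condition).
- Later calls: 4 in each arm, at 12, 16, 22 and 30 weeks (Booster and follow-up phone calls).
- Preferred group size: 5–12 participants (Recruitment and randomization procedures).

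**Intervention phase**
- SMG contact time per participant = 7 × 90 = 630 minutes = 10.5 hours, at full attendance.
- Number of contacts: SMG 7, BOOK 2.
- Length each BOOK call would need in order to match = 630 / 2 = 315 minutes. No ordinary telephone call comes near this, so the conclusion does not depend on a guess about call length.

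**Whole study**
- SMG contacts = 7 + 4 = 11.
- BOOK contacts = 2 + 4 = 6.
- If the four later calls are equally long in both arms, they add the same time to each side and leave the intervention-phase difference in minutes unchanged.

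**Kind of contact**

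| | SMG | BOOK |
|---|---|---|
| Intervention phase | Group sessions with facilitator and peers; help with a personal plan | Two individual calls; no therapeutic component, no goals or plan |
| Later calls | Review of the plan, encouragement, problem-solving | Same number and timing; no such content described |

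Even the later calls are therefore matched in number and timing, not in content.

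**Sensitivity to how contact is counted**

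Group minutes are shared, so one can instead divide facilitator time by group size:
- Group of 12: 630 / 12 = 52.5 facilitator-minutes per participant.
- Group of 5: 630 / 5 = 126 facilitator-minutes per participant.
- Call length at which two BOOK calls would match: 52.5 / 2 ≈ 26 minutes, to 126 / 2 = 63 minutes.

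On this narrower measure the gap is much smaller, and long calls could close it. The measure leaves out what the participant experiences, which is 630 minutes in company, and it gives no weight to peer contact, of which BOOK has none. The counts of 7 against 2 do not change.

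**The case against.** The strongest reply is that the trial never undertakes to separate skills from attention. The stated aim is to compare the SMG intervention with a control condition, the abstract calls that control education-only, and the Discussion again speaks of a treatment programme against a control. A minimal-contact education arm is a legitimate comparator for evaluating a programme, and the paragraph that makes the attention claim also discloses the contact that BOOK receives. This stands. It means that the comparison is sound and that the fault lies in one sentence and what may be built on it.

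A second reply concerns size. Much of the 630 minutes is active treatment, such as exercise and relaxation practice, and not attention alone. The relaxation tape, tubing and gel packs are treatment materials and say nothing about attention. Both points stand. The 630 minutes is total contact, not a measure of non-specific effect, and the materials are not counted here.

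A third reply is that the primary test is a group effect over three assessments, with power worked out for 12 months, after four matched calls. This reduces the emphasis on the post-intervention result but does not remove it, since that assessment enters the same group effect.

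A fourth reply is that expectations are rated before allocation is known, class attendance is recorded, and baseline variables that differ between groups or correlate with outcome enter the model. These help. Adjusting for a baseline rating cannot, however, remove the effect of contact received afterwards, and how the ratings are tabulated is a matter for the full plan or the results paper.

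Two stronger readings are tempting. A reader might infer that the trial cannot test SMG at all; the documents do not support this, because facilities are randomised between two clearly described packages. A reader might also want a ratio of contact time between the arms; the documents give no call length, so any such figure would rest on an assumption, and none is given here.

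**Conclusion.** The concern holds in a limited form. For the intervention phase the stated control for attention is not a property of the design: 7 contacts totalling 630 minutes in a group, against 2 calls of unstated length, and 11 contacts against 6 over the study. The later calls are matched in number and timing.

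No estimate, test, error rate or power figure is affected. The effect is on attribution. With two arms and this imbalance, a difference in self-reported outcomes can be credited to SMG as delivered, but not to skills over attention. How much of any difference would come from contact cannot be judged from the documents.

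The conclusion assumes that sessions run to their stated length and that the two BOOK calls are the only facilitator contact in that arm before the post-intervention assessment. Lower attendance would reduce 630 minutes for some participants; it would not make the arms equal in kind of contact.

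**What to change.** In the section on the educational book control condition, replace the attention claim. Describe BOOK as an information control with minimal contact, and state that attention is matched only for the follow-up calls at 12, 16, 22 and 30 weeks, and there only in number and timing.

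State that the conclusion on the primary outcome is limited to the effect of the SMG package (skills, group and facilitator contact, and materials) against a workbook plus calls, with no attribution to skills over attention. The results on beliefs and coping under Hypotheses 2 and 3 should be worded within the same limit.

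This needs no new arm, no new data and no change to the analysis. The cost is a few sentences and a narrower conclusion.
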